## Abstract

**Background:**

Evidence supports several countries introducing legislation to allow cannabis-based medicine as an adjunctive treatment for the symptomatic relief of chronic pain, chemotherapy-induced nausea, spasticity in multiple sclerosis (MS), epileptic seizures, depression, and anxiety. However, clinical trial participants do not represent the entire spectrum of disease and health status seen in patients currently accessing medicinal cannabis in practice.

**Objective:**

This study aims to collect real-world data to evaluate health-related quality of life in patients prescribed medicinal cannabis oil and describe any differences over time, from before starting therapy to after 3 and 12 months of therapy.

**Methods:**

Adult patients newly prescribed medicinal cannabis oil by authorized prescribers and under the Special Access Schemes across Australia will be screened for eligibility and invited to participate. A sample size of 2142 is required, with a 3-month follow-up. All participants will complete the EuroQol 5-Dimension; European Organization for Research and Treatment of Cancer Quality of Life Questionnaire-30; Depression, Anxiety, and Stress Scale-21; Patients’ Global Impression of Change; Patient-Reported Outcomes Measurement Information System (PROMIS) Short Form (SF) version 1.0: Sleep Disturbance 8b; and PROMIS SF Fatigue 13a questionnaires. Patients with chronic pain conditions will also complete the PROMIS SF version 1.0: Pain Intensity 3a and PROMIS SF version 1.0: Pain Interference 8a. Patients with movement disorders will also complete Quality of Life in Neurological Disorders (Neuro-QoL) SF version 1.0: Upper Extremity Function (Fine Motor and Activities of Daily Living) and if chorea is indicated, the Neuro-QoL SF version 2.0: Huntington’s Disease health-related Quality of LIFE-Chorea 6a. All questionnaires will be administered at baseline, 2 weeks (titration), monthly up to 3 months, and then every 2 months up to 1 year.

**Results:**

Recruitment commenced in November 2020. By June 2021, 1095 patients were screened for the study by 69 physicians in centers across 6 Australian states: Australian Capital Territory, New South Wales, Queensland, South Australia, Victoria, and Western Australia. Of the patients screened, 833 (39% of the target sample size) provided consent and completed baseline questionnaires. Results are expected to be published in 2022. Results of this study will show whether patient-reported outcomes improve in patients accessing prescribed medicinal cannabis from baseline to 3 months and whether any changes are maintained over a 12-month period. This study will also identify differences in improvements in patient-reported outcomes among patients with different chronic conditions (eg, chronic pain, MS, epilepsy, Parkinson disease, or cancer).

**Conclusions:**

This protocol contains detailed methods that will be used across multiple sites in Australia. The findings from this study have the potential to be integral to treatment assessment and recommendations for patients with chronic pain and other health indicators for accessing medicinal cannabis.

**Trial Registration:**

Australian New Zealand Clinical Trials Registry: ANZCTRN12621000063819; https://www.anzctr.org.au/Trial/Registration/TrialReview.aspx?id=380807&isReview=true

**International Registered Report Identifier (IRRID):**

DERR1-10.2196/32327

## Introduction

### Medicinal Cannabis

With the first accounts of cannabis being used as medicine dating back to China in 2600 BC, its use for medicinal purposes has been recorded on nearly every continent throughout history [1]. Many countries criminalized the consumption of cannabis in the 1900s, consequently limiting the potential therapeutic benefits and research into medicinal use. However, the identification of cannabinoids, cannabidiol, and Δ9-tetrahydrocannabinol as analgesics in 1940 refocused attention on using cannabis-based medicine as an adjunctive treatment for the symptomatic relief of chronic pain [1]. The last 2 decades have seen an increase in medicinal cannabis research, particularly in response to growing concerns about the misuse and adverse events associated with opioids [2], including increased risk of endocrinopathy, bowel dysfunction, cognitive decline, hospitalization, and death from overdose [3]. Research to date has provided sufficient evidence for several countries to introduce legislation allowing its use for medicinal purposes. These policies help to avoid the potential risk of cannabis abuse by self-medicating [4] and enable appropriate monitoring of possible adverse drug-drug interactions [5]. In 2020, there were approximately 400,000 medicinal cannabis patient registrations in Canada [6], more than 60,000 in Germany [7], and more than 25,000 in Australia [8].

Evidence from randomized controlled trials indicates that medicinal cannabis can reduce chronic pain [9-12], neuropathic pain [13], cancer pain [14], chemotherapy-induced nausea [15], spasticity in multiple sclerosis (MS) [16,17], epileptic seizures [18], depression [10,12], anxiety [12], improve sleep [19], and reduce opioid prescription numbers [20]. However, depression, anxiety, and sleep problems may be exasperated with formulations containing high ratios of Δ9-tetrahydrocannabinol [21], and for some health indications, using medicinal cannabis in a *real-world* setting may be confounded by drug-drug interactions [5]. This supports the need for oversight by health care professionals and further research collecting *real-world* evidence.

### Why Patient-Reported Outcomes Are Important

A patient-reported outcome (PRO) is any report coming directly from patients without interpretation by physicians or others about how the patient feels in relation to a health condition and its therapy [22]. PROs can include symptoms, aspects of functioning, multidimensional constructs such as health-related quality of life (HRQL), and perceptions of treatment. PROs are regarded as the gold standard for assessing pain [23] and are particularly important end points to include when assessing patients with chronic conditions where the primary aim is to palliate symptoms [24]. These patient reports were captured and quantified by PRO measures (PROMs) using validated and reliable standardized questionnaires that allow comparisons between treatment groups and within groups over time. The wide acceptance of PROM-based evidence by regulatory bodies is reflected in the Australian Commission on Safety and Quality in Health Care’s support of the use of PROMs to drive quality improvement [25] and the US Food and Drug Administration’s approval of PROs to support product labeling claims [26].

### Health Indications for Accessing Medicinal Cannabis

The Australian Therapeutic Goods Administration (TGA) currently approves Special Access Scheme (SAS) applications from health care providers who provide a clinical justification for prescribing medicinal cannabis where conventional therapies have failed [8]. There are no TGA-imposed restrictions on the types of health conditions; however, prescriptions are more commonly sought for chronic pain and spasticity from neurological conditions.

#### Chronic Pain

Chronic pain is a widespread health issue broadly defined as pain that lasts or recurs for more than 3 months [27] and is categorized as *chronic primary pain*—a disease in its own right such as nonspecific low-back pain—or as *chronic secondary pain* initiated as a symptom of an underlying disease, such as cancer-related pain or neuropathic pain [28]. In Australia, more than 15% of the adult population lives with persistent chronic pain or recurring pain lasting longer than 6 months [29]. In the United Kingdom, as many as 35% of adults experience some level of chronic pain lasting more than 3 months, with more than 10% reporting moderate to severely limiting chronic pain [30]. In 2016, the Centers for Disease Control and Prevention reported that 20% of US adults had chronic pain and 8% experienced chronic pain that severely interfered with daily functioning on most days or every day for a 6-month period [31].

Cancer-related pain is experienced by approximately one-third of patients with cancer at diagnosis and during treatment and by approximately three-fourths of patients with advanced-stage cancer. However, 10%-15% of the patients are nonresponsive to conventional pain therapy [32]. Residual tissue damage from cancer and cancer treatment often results in chronic pain in cancer survivors, which lasts many years after treatment [33].

Neuropathic pain, which is caused by a lesion or disease of the somatosensory nervous system [34], is experienced by approximately 8% of the population [35] and approximately 86% of the patients with MS [36]. Neuropathic pain is associated with higher rates of unemployment [35], poor physical, psychological, and social functioning, significantly impaired overall HRQL and sleep, and higher depression and anxiety than those with other chronic pain and those without pain [37]. Less than 35% of the patients with neuropathic pain respond to conventional therapy [38], whereas others often receive incomplete pain relief along with conventional treatment-related side effects [39].

The prevalence of chronic pain increases dramatically in patients receiving palliative care [40,41]. A study of patients in palliative care clinics in the United States found that most of them were admitted with unrelieved pain and that chronic pain assessment and management were inadequate [42]. In addition, one-third of the patients receiving palliative care who experienced pain were significantly more likely to also suffer from depression [41], report insufficient sleep [43], and were at a higher risk of opioid misuse [40]. Effective pain and symptom management aimed at reducing suffering and improving overall HRQL are the primary goals of palliative care.

#### Neurological and Movement Disorders

MS is a chronic inflammatory and demyelinating neurodegenerative disorder that often involves symptoms such as spasms, tremors, pain, fatigue, bladder dysfunction, cognitive impairment, depression, and impairments in swallowing, speech, vision, and balance [44]. In 2018, MS Research Australia reported an estimated 24,600 Australians with MS, and, on average, their overall HRQL was 31% less than the Australian population norm (measured by the health state utility valuation) [45]. As a currently incurable and often progressive condition, treatment and management largely focus on improving the quality of everyday life by relieving symptoms [44]. A systematic review of reviews conducted in 2018 on the effects of cannabidiol, Δ9-tetrahydrocannabinol, or cannabidiol and Δ9-tetrahydrocannabinol formulations in treating MS symptoms found sufficient evidence supporting cannabinoids in relieving both pain and spasticity symptoms [46].

Epilepsy is a chronic neurological disease characterized by 2 or more unprovoked seizures and affects approximately 50 million people worldwide [47]. High-quality evidence from randomized clinical trials suggests that cannabidiol reduces seizure frequency; however, further examination of PROs is needed to assess whether cannabidiol interacts with other antiseizure medications to produce unwanted side effects [48].

### Critical Gaps in Knowledge About HRQL in Patients Accessing Medicinal Cannabis

PRO assessment can assist health care professionals in monitoring treatment outcomes over time from patients’ perspectives. In 2020, there were no published results from a centralized PRO data collection for a large sample of patients accessing prescribed medical cannabis within Australia that covers all approved health indications using a comprehensive battery of PROMs. Participants studied under controlled clinical trial environments have not always been representative of the entire spectrum of disease and health status seen in people currently accessing medicinal cannabis in practice [49]. Therefore, although clinical trials provide evidence of the efficacy of medicinal cannabis, the true gauge of how effective it is in practice comes from real-world evidence from patients across all health conditions receiving prescribed medicinal cannabis [49]. Real-world data are needed to develop a scientific evidence base to inform regulation and policy making [7].

A scoping review that we conducted identified the following limitations in the current evidence on PROs for medicinal cannabis:

Very few studies have collected PRO data longitudinally, including baseline, maintenance, and long-term use data [4].A large proportion of cannabinoid research was focused on pharmacokinetic, animal, and preclinical studies.Many cannabinoid clinical studies include case studies [4] or have small sample sizes [50].Early studies did not use the currently recommended individualized dosing titration paradigm of starting low and gradually escalating to achieve optimal effects [50].Formulations studied may not reflect current commercially available cannabinoid products [11].Many PROMs used have limited validity in the health conditions assessed [12].Very few clinical studies used comprehensive pain assessments.

Therefore, the real-world collection of a comprehensive suite of PROs in a large sample of people across all health conditions, as approved by the TGA, accessing current formulations of prescribed medicinal cannabis in Australia is needed to enable clinically relevant assessment and provide ongoing evidence for decision-making both in practice and at a policy level.

### Objectives

The aim of this study is to evaluate PROs in patients who are prescribed medicinal cannabis by authorized prescribers and under the SAS across clinics within Australia. The findings from this study have the potential to be integral to treatment assessment and recommendations for chronic pain sufferers and other patients with health indicators for accessing medicinal cannabis.

#### Primary Objective

The primary objective of this study is to describe changes in the PROs (HRQL, pain, fatigue, sleep, anxiety, and depression) from baseline to 3 months for a large cohort receiving medicinal cannabis.

#### Secondary Objectives

The secondary objectives of this study are to describe changes in PROS (HRQL, pain, fatigue, sleep, anxiety, depression, and physical functioning) from baseline up to 12 months and to describe differences between patients accessing medicinal cannabis with different chronic health conditions, including, but not limited to, chronic pain, MS, epilepsy, Parkinson disease, and cancer.

#### Exploratory Objectives

The exploratory objectives of this study are to explore (1) which individuals are more likely to have lower symptom burden and greater HRQL, (2) associations among PROs, with the hypothesis that a high symptom burden is associated with poorer HRQL, and (3) associations between PROs and resource and medication use over time, with the hypothesis that lower symptom burden is associated with reduced health care–resource use and reduced use of opioids and other prescribed medications for managing symptoms.

#### Hypotheses

The study includes 3 hypotheses: (1) PROs will improve from baseline to 3 months in patients accessing medicinal cannabis, (2) improvements in PROs at 3 months will be maintained over a 12-month period, and (3) no differences in PROs will be observed between patients being treated for different conditions (eg, chronic pain, MS, epilepsy, Parkinson disease, or cancer).

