### Analyses and Statistical Considerations

#### Analysis Set

All analyses will be performed using SPSS software (version 26.0; IBM Corp). Baseline demographic and clinical data will be summarized descriptively for all patients registered for the study. Categorical data will be presented as frequencies and percentages. For continuous scale data, mean, SD, median, 25th and 75th percentiles, and minimum and maximum scores will be presented.

PRO analyses will explore changes over time using mixed linear models. Subgroup analyses will compare differences in PROs between underlying conditions, dose, and duration of pain and over time using linear mixed models.

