#### Statistical Considerations

A comprehensive PRO-specific statistical analysis plan will be produced by the study statistician. The key considerations include the following:

PRO questionnaire responses will be scored into PRO scales for outcome analysis according to standard scoring algorithms provided by the questionnaire developers and custodians.Rates and reasons for missed PRO assessments will be summarized to assess likely missing data mechanisms against missing data assumptions of statistical modeling.For each PRO, all participants with a score for that PRO at baseline and at least one time point after starting medicinal cannabis will be analyzed.Linear mixed models will be used to compare groups in their PRO scores, adjusted for their PRO levels at baseline and with additional covariates such as duration of pain, previous cannabis use, use of other medications, and overall and prespecified subgroups.If the scores are highly skewed, a suitable transformation will be sought to achieve normality.As there are several PRO scales and time points and correlation among them is anticipated, statistical significance levels will be adjusted using an appropriate method [82].The clinical significance of differences in the PRO questionnaires will be interpreted using existing guidelines (eg, QLQ-C30) [83], maintaining the overall type 1 error at 5% or less.

Missing items within the PRO questionnaires are not expected. This is because of the web-based administration platform alerting participants of missed items and the requirement to complete those items before progressing to the next page. Only those participants who complete at least 2 questionnaires (baseline and one other) will be included in the analysis. Single missed assessments will be imputed using the last value carried forward technique, that is, no change from that individual’s last assessment. Pattern mixture models will be used to impute scores for missed assessments based on recorded reasons [84].

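### Hypothesis 3 predicts no differences between conditions, but the only stated analyses look for differences, so a non-significant result cannot support it and could be misread as confirmation

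*Protocol article*

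**What the plan says.** The Hypotheses section lists three predictions. The third is that "no differences in PROs will be observed between patients being treated for different conditions", with chronic pain, multiple sclerosis, epilepsy, Parkinson disease and cancer as examples. The second is that "improvements in PROs at 3 months will be maintained over a 12-month period".

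The analysis of conditions is given under Analysis Set: "Subgroup analyses will compare differences in PROs between underlying conditions, dose, and duration of pain and over time using linear mixed models". The analysis over time is given there too: "PRO analyses will explore changes over time using mixed linear models". Statistical Considerations adds that, because there are several scales and time points, "statistical significance levels will be adjusted using an appropriate method". It also says that "The clinical significance of differences in the PRO questionnaires will be interpreted using existing guidelines", "maintaining the overall type 1 error at 5% or less".

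The matching secondary objective is worded more softly: "to describe differences between patients accessing medicinal cannabis with different chronic health conditions". The only sample-size calculation concerns change over time to 3 months in the whole cohort. No equivalence margin, no criterion for maintenance and no minimum size per condition is stated.

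**The concern.** Hypothesis 3 is worded as a null. A comparison designed to detect differences can count against it but cannot count for it, because failing to detect a difference is also what too few patients would produce. The usual safeguards then work in reverse. Multiplicity adjustment protects against false claims of a difference, but here each tightening of the threshold makes it easier to find nothing. The less informative the data on a condition, the more readily the prediction appears to be met.

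Unequal group sizes are plausible. Every eligible patient is invited without quotas, and the Introduction notes that prescriptions are sought more often for chronic pain and neurological spasticity. The Objectives section expects the findings to inform treatment recommendations, so an unsupported statement that the condition treated makes no difference could carry weight.

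**Working it through.** **The plan's own figure.** Inputs from the sample-size section: effect size 0.1, two-sided 1% level, 95% power, 20% loss. For a paired (one-sample) comparison:

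- Normal approximation: n = (2.576 + 1.645)² / 0.1² = 1782 after rounding up.
- Noncentral t: n = 1785.
- 1785 × 1.2 = 2142, the stated figure.

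So 2142 is sized for change over time in the whole cohort. It says nothing about comparisons between conditions.

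**Between-condition comparison.** The article gives no group sizes. Assumptions: a reference condition of 1000 patients, a smaller condition of n, SD of change 1, and one unadjusted contrast.

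- SE = √(1/1000 + 1/n). For n = 50, SE = √0.021 = 0.145.
- Chance of missing a true difference d ≈ Φ(z − d/SE), where z is the two-sided critical value.
- For d = 0.3: d/SE = 2.07. At 5%, Φ(1.96 − 2.07) = 0.46. At 1%, Φ(2.576 − 2.07) = 0.69.
- 90% confidence interval half-width = 1.645 × 0.145 = 0.24.

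| Smaller group (vs 1000) | 0.2 SD missed, 5% | 0.3 SD missed, 5% | 0.3 SD missed, 1% | 90% CI half-width (SD) |
|---|---|---|---|---|
| 20 | 86% | 74% | 89% | 0.37 |
| 50 | 72% | 46% | 69% | 0.24 |
| 100 | 52% | 18% | 39% | 0.17 |
| 200 | 27% | 3% | 10% | 0.13 |

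The 1% level is the one in the sample-size section. The multiplicity method is cited but not named, so the level that would apply to these comparisons is unknown.

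**What a claim of no difference would need.** Two one-sided 5% tests (equivalent to a 90% interval), 80% power, true difference zero, margin m, reference group 1000:

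- n = 1 / [(m / (1.645 + 1.282))² − 1/1000].
- m = 0.2 SD needs 273 in the smaller group; 0.3 SD needs 106; 0.5 SD needs 36.
- With n = 50, the half-width of 0.24 already exceeds 0.2, so equivalence within 0.2 SD could not be shown whatever the estimate.

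**Hypothesis 2.** This is a within-patient question in the whole cohort. Paired non-inferiority at one-sided 2.5% with 80% power and a margin of 0.1 SD of the change needs (1.960 + 0.842)² / 0.1² = 785 pairs. That is 785 / 2142 = 37% of the planned baseline sample. Retention at 12 months is not stated, but low power is not the main issue here. What is missing is a criterion for how much loss still counts as maintained.

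**The case against.** The strongest reply is that the article is descriptive. The secondary objectives are to describe, the models explore, and a PRO-specific analysis plan is promised that would normally hold margins and decision rules. The clinical-significance guidelines are cited in general terms and exclude neither between-condition nor over-time comparisons, so differences will not be read by p-value alone.

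Much of this stands. A reader might infer that the investigators intend to treat p above the cut-off as proof of no difference. No section says so. The absence of a margin is, on its own, ordinary analysis-plan detail.

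What remains is what the article itself fixes: a hypothesis worded as a null, paired only with difference-type comparisons and adjusted significance levels. The guidelines are cited for interpreting differences and are not linked to a claim that there are none.

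A reader might also extend the small-group argument to hypothesis 2. That does not follow, because hypothesis 2 concerns within-patient change in the whole cohort. Moreover, if maintained means still better than baseline, an ordinary difference test can support it, and low power would work against it.

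Finally, the group sizes and SD are assumed, and the planned models adjust for baseline and covariates, which could improve precision. The 0.1 effect size in the sample-size section belongs to whole-cohort change on the insomnia scale and is not a yardstick for differences between conditions.

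**Conclusion.** The point holds for hypothesis 3. As stated, a non-significant between-condition comparison cannot support the prediction and could be mistaken for confirmation. With an assumed 50 against 1000 patients and SD 1, a real 0.3 SD difference would go undetected 46% of the time at 5% and 69% at 1%. The problem fades as the smaller group grows: at 200 the 5% figure is 3%. The size therefore depends on the case mix, which the article does not give, but the logical mismatch does not.

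For hypothesis 2 the point is secondary: maintenance has no stated criterion. The documents do not support saying that either hypothesis will be declared confirmed by non-significance, or that hypothesis 2 suffers from small groups.

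**What to change.** Choose one of two routes for hypothesis 3 and record it in the analysis plan:

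1. Restate it as estimation: report between-condition differences in change with confidence intervals, read against clinical thresholds.
2. Keep the claim, but make it only when the 90% confidence interval for the between-condition difference in change lies wholly within the small-difference threshold of the cited guidelines for that scale. Name the threshold for each scale in advance; the article gives the QLQ-C30 only as an example.

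Under either route, report an interval that reaches beyond the threshold without showing a difference as inconclusive, and never infer no difference from p above the cut-off.

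For hypothesis 2, read maintenance from the confidence interval for the 12-month minus 3-month change (T8 minus T4), requiring it to exclude worsening by the same threshold.

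The change is to wording only and needs no new data. The downside is that small condition groups will be reported as inconclusive.
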